## Abstract

**Background:**

Individuals with incomplete spinal cord injury (iSCI) often face significant impairments in sitting balance and mobility due to trunk instability. These challenges can severely impact functional abilities, participation in daily activities, and overall quality of life (QoL). Studies have demonstrated the potential of virtual reality (VR) training to improve sitting balance in individuals with iSCI. Furthermore, sensory electrical stimulation (SES) has shown positive effects on sitting balance in various neurological populations. However, research exploring the combined effectiveness of virtual reality and sensory electrical stimulation on sitting balance and QoL, specifically within the iSCI population, remains limited.

**Methodology:**

This study will be an assessor-blind, parallel, two-group, randomized controlled trial that aims to evaluate the effectiveness of SES-augmented VR-based balance training on sitting balance and QoL in individuals with iSCI. A total of 22 participants with iSCI, with a neurological level of injury between T6 and T12, will be recruited from the rehabilitation department at the Indian Spinal Injuries Centre, adhering to inclusion criteria. Participants will be randomly assigned to one of two groups using a 1:1 allocation ratio. The experimental group will engage in VR-based balance training along with SES application, while the control group will engage solely in VR-based balance training. Both groups will receive interventions consisting of 30-min sessions five times a week for a duration of 4 weeks.

**Outcome measures:**

The assessment of sitting balance will be done using the modified functional reach test (mFRT) and the star test using the Tecnobody ProKin 252 trunk sensor. Additionally, the International Spinal Cord Society Quality of Life Basic Data Set (ISCoS QoL BDS) version 1.0 will be used to measure QoL.

**Discussion:**

The effectiveness of the SES-augmented VR-based balance training will be evaluated based on the changes in the mFRT, star test (ProKin 252 trunk sensor), and ISCoS QoL BDS version 1.0 following 4 weeks of intervention. This trial aims to enhance understanding of how SES-augmented VR training can improve sitting balance and QoL in individuals with iSCI.

**Trial registration:**

The trial is registered with the Clinical Trials Registry—India on 18th April 2024 with registration number CTRI/2024/04/065897.

**Supplementary Information:**

The online version contains supplementary material available at 10.1186/s13063-026-09837-7.

## Background

Spinal cord injury (SCI) is a debilitating neurological condition characterized by sensory, motor, autonomic, or bowel dysfunction caused by damage to neuronal elements of the spinal cord. Its incidence ranges from 8 to 246 cases per million worldwide, whereas the prevalence ranges from 236 to 1298 per million [1], with approximately 20,000 new cases documented annually in India [2]. Countries such as India are at high risk, with an average age group ranging from 26.8 to 56.6 years with a male-to-female ratio of 4:1 [1]. It often leads to a profound disability that negatively impacts physiological, physical, or psychological well-being and restricts employment opportunities even after the individual has reintegrated into the community.

Following SCI, maintaining sitting balance is essential for performing activities of daily living. Approximately 70–80% of individuals with SCI experience impaired or no trunk control, which adversely affects their ability to maintain sitting balance and overall quality of life (QoL) [3]. Trunk instability is a significant concern for individuals with SCI [4], as it impacts their ability to perform everyday tasks such as bed movements, unsupported sitting, and self-care activities [5, 6]. Additionally, it can lead to secondary complications such as pressure sores [7], spinal deformities [8], and pulmonary dysfunction [5]. Furthermore, individuals with SCI are also at a higher risk of falls even during stationary sitting, leading to fall-related pain and bone fractures [9]. Consequently, QoL in individuals with SCI is closely linked to their dynamic sitting balance and ability to sit unsupported [10], a relationship that becomes increasingly important over time post-injury [8].

Given these challenges, recovery of trunk control is essential for those experiencing difficulties with sitting balance [11]. However, research investigating sitting balance in individuals with incomplete spinal cord injury (iSCI) remains limited [10]. Conventional methods for maintaining sitting stability often involve belts, straps, and customized seating adaptations designed to stabilize the trunk, prevent falls, and facilitate upper limb function [12]. Unfortunately, these techniques can restrict dynamic mobility and hinder the ability to reach for objects [13].

In individuals with iSCI at thoracic levels T6–T12, injury to the descending motor tracts disrupts supraspinal control of key trunk musculature, impairing the voluntary activation of erector spinae and other postural muscles essential for maintaining sitting posture. At the same time, damage to ascending sensory pathways also reduces proprioceptive and cutaneous afferent input, impairing both anticipatory postural adjustments preceding voluntary movement and reactive responses necessary to counter external perturbations. The combined impairment of descending motor drive and ascending sensory feedback at these thoracic levels results in a deficit in neuromuscular control [14, 15].

The recovery of sitting balance is a primary objective in rehabilitation programs for individuals with iSCI. While research on effective balance training protocols for individuals with iSCI is scarce, recent advancements and the existence of many strategies like electrical stimulation [16], non-invasive spinal stimulation [9], community exercise programs [17], functional electrical stimulation [18], and virtual reality (VR) [19, 20] demonstrate improvement in mobility along with postural control. Methods utilizing VR have demonstrated positive results for training balance across various neurological populations. This technology provides a user-computer interface that facilitates real-time simulation of activities or environments, allowing user interaction through various sensory modalities and enhancing engagement and motivation during rehabilitation. Previous studies utilizing game-based exercises within VR have shown improvements in dynamic sitting balance among individuals with SCI [21–23].

Sensory electrical stimulation (SES) involves the use of low-intensity currents (below, at, or only just above the sensory threshold), which does not induce any visible muscle contraction and provides only sensory information. The beneficial effects of SES are thought to occur at the peripheral (sensory receptor sensitivity), spinal (spinal motoneural excitability), and supraspinal (cortex reorganization or adaptation) levels. SES appears to be particularly useful to reinforce or restore the postural function in the immediate/concurrent, acute, or chronic applications in pathological populations. Studies have already shown that SES is effective at improving postural balance in various neurological conditions, such as stroke and cerebral palsy [24, 25].

The integration of VR and SES may address the deficit in neuromuscular control. VR promotes neuroplasticity through enriched, multisensory, goal-directed motor tasks that engage residual pathways, reinforce motor relearning, and provide augmented visual and proprioceptive feedback within task-specific environments [19, 20]. Concurrently, SES enhances peripheral afferent input and modulates spinal excitability, thereby facilitating sensorimotor reorganization [24, 25]. When delivered simultaneously, these modalities may act synergistically, with SES amplifying afferent sensory input and VR providing a task-specific motor context, thereby facilitating neuroplastic adaptations.

Therefore, this study aims to investigate the effectiveness of SES-augmented VR-based balance training on sitting balance and QoL in individuals with iSCI. It is hypothesized that significant improvement in sitting balance and QoL will be noticeable after 4 weeks of SES-augmented VR-based balance training when compared with participants receiving VR-based balance training alone.

## Materials and methods

A clinical trial is designed to evaluate the effectiveness of the SES-augmented VR-based balance training on sitting balance and QoL in individuals with iSCI.

### Patient and study design

An assessor-blind, parallel, two-group, randomized controlled trial with equal subject allocation (1:1) will be undertaken. A sample of 22 participants with iSCI will be recruited from the inpatient and outpatient rehabilitation departments of the Indian Spinal Injuries Centre, New Delhi, India. All participants will be provided with information sheets, and written consent will be obtained by the principal investigator before recruitment. The demographic details will be obtained, and the participants will be selected based on the eligibility criteria after neurological examination (Table 1).

**Table 1 Tab1:** Eligibility criteria

	Criteria
Inclusion criteria	Diagnosis of spinal cord injury > 6 months T6–T12 level of injury ASIA B, C, D Age between 18 and 60 years Ability to sit unsupported for 10 s and a minimum of 90° shoulder flexion
Exclusion criteria	Uncorrected hearing or visual impairment that interferes with the ability to perceive visual stimuli, follow verbal instructions, or safely participate in the virtual reality-based intervention Deformity of upper limb, any other psychiatric, neurological, or musculoskeletal impairment History of severe recent urinary tract infection or autonomic dysreflexia Refusal or inability to provide informed consent and inability to follow commands Additional exclusion criteria (sensory electrical stimulation group): 1. Pressure sores ≥ grade 2 at the site of stimulation according to National Pressure Ulcer Advisory Panel Classification 2. Cardiac pacemaker

The participants will be randomly assigned to any of the two groups—the virtual reality-based balance training along with sensory electrical stimulation (VR-SES) group and the virtual reality-based balance training (VR) group. Both groups will receive intervention sessions five times per week for 4 weeks.

The Departmental Research Review Committee (DRRC) and Research Review Committee (RRC) of the research department of the Indian Spinal Injuries Centre hold the legal liability and keep the check and record of all potential recruits and monitor the data collection throughout the intervention. The members of DRRC, along with the consultants and physiotherapists in the hospital, provide day-to-day support to all aspects of the local organization of the trial. The day-to-day conduct of the trial, including participant recruitment, monitoring, intervention implementation, and protocol adherence, will be overseen by the principal investigator under the supervision of the guides. The Trial Management Group (TMG) will conduct meetings monthly to ensure oversight of trial progress and operational issues. The DRRC will conduct audits of the trial every 6 months, while the Institutional Ethics Committee (IEC) will undertake an annual review to ensure compliance with the approved protocol and ethical standards. A Data Monitoring Committee (DMC) will not be constituted, as this study involves a low-risk intervention. This research protocol is consistent with the current Consolidated Standards of Reporting Trials (CONSORT) guidelines (Fig. 1) and follows the Standard Protocol Items: Recommendations for Interventional Trials (SPIRIT schedule) (Table 2) [26] and is developed based on the SPIRIT checklist (Additional document 1). A visual description of the study regarding enrollment, assessments, and interventions is shown in Table 2.

**Fig. 1 Fig1:**
[figure not shown]
CONSORT (Consolidated Standards of Reporting Trials) flowchart. VR-SES group, virtual reality-based balance training along with sensory electrical stimulation; VR group, virtual reality-based balance training

**Table 2 Tab2:**
[figure not shown]
Schedule of enrollment, interventions, and assessments according to the Standard Protocol Items: Recommendations for Interventional Trials guideline

*Abbreviations*: *VR-SES group* Virtual reality-based balance training along with Sensory electrical stimulation, *VR group* Virtual reality-based balance training, *mFRT* Modified functional reach test, *ISCoS Qol BDS V1.0* International Spinal Cord Society Quality of Life Basic Data Set Version 1.0.

Baseline assessments (T_0_) will be done before group allocation. Post-intervention assessments of both groups (T_1_) will be done after 4 weeks of intervention to detect potential long-term effects.

### Ethical considerations

The enrolled participants will be informed orally and in writing about the purpose of this trial, its potential risks, the benefits of participation, and their right to withdraw from the trial at any point during the study. A written informed consent signed by the participants will be taken from those who are willing to participate in the study.

The data of the participants will be collected, documented, and managed confidentially using the paper-based entry data sets. Only all the authors related to the trial will have access to the final trial dataset. The masked datasets analyzed during the current study and statistical code will be available from the corresponding author upon reasonable request. The study protocol has been approved by the IEC of the Indian Spinal Injuries Centre and is registered with the Clinical Trials Registry—India (CTRI).

Any protocol deviations will be fully documented using a breach report form. In case of any important modification or amendment, the principal investigator will discuss the changes with the research team and the amendment will be formally documented and the revised protocol will be submitted to the RRC and IEC for approval prior to implementation. All amendments will also be updated in the CTRI.

Patients and the public will not be involved in the design, conduct, or reporting plans of this study.

### Randomization

Eligible individuals will be assigned randomly to either the experimental or control group. Randomization will be performed using a computer-generated randomization sequence generated by the Random Allocation Software, using a 1:1 allocation ratio.

To ensure concealment, the allocation sequence will be marked sequentially and sealed in opaque envelopes. An individual not associated with the study will sequentially open the numbered envelopes to reveal the participant’s group allocation.

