## Statistics

### Sample size

A priori sample size estimation was done using the G*Power 3 software (3.1.9.6, Heinrich-Heine-Universität Düsseldorf, Düsseldorf, Germany) by considering the mFRT as the primary outcome measure. The total sample size was calculated at 20 by using an *α* level of 0.05 and a power of 80%. The potential loss to attrition was estimated at 10%. Hence, the total sample size was 22.

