## Discussion

The recovery of sitting balance is one of the primary and essential aims of rehabilitative programs in individuals with iSCI. Retraining sitting balance is challenging for healthcare professionals dealing with iSCI. The trial will provide information about the effectiveness of SES-augmented VR-based balance training in improving sitting balance and QoL in individuals with iSCI. The training is expected to enhance sitting balance and QoL in individuals with iSCI. To the best of our knowledge, no study until now has examined the effectiveness of SES-augmented VR-based training on sitting balance and QoL in the iSCI population.

This trial is designed to meet the methodological demand for adequate randomization, allocation concealment, and blinding of outcome assessors and statisticians. The trial will be reported according to the CONSORT guidelines. This study has several limitations. The recruitment of the participants will be done through a sample from one center; it may limit the generalizability of the findings. The sample size, calculated based on the primary outcome measure, may limit the power to detect differences in secondary outcomes. Therefore, secondary outcome findings should be interpreted as exploratory and hypothesis-generating. The lack of long-term follow-up may limit the ability to assess the durability of the intervention effects. In future, multi-center trials incorporating stratified block randomization are recommended to strengthen comparability.

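### With 22 participants of mixed severity and no stratification described, the unadjusted mFRT test leaves chance baseline imbalance uncorrected; adjust for baseline mFRT

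*Protocol article*

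**What the plan says.** Patient and study design sets out a "randomized controlled trial with equal subject allocation (1:1) will be undertaken", with 22 participants. Table 1 admits ASIA B, C and D and injury levels T6 to T12.

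The Randomization section gives the sequence in one sentence: "Randomization will be performed using a computer-generated randomization sequence generated by the Random Allocation Software, using a 1:1 allocation ratio". Sealed, numbered, opaque envelopes follow. It mentions neither strata nor blocks, and it does not call the list simple.

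Among the limitations, the Discussion says: "In future, multi-center trials incorporating stratified block randomization are recommended to strengthen comparability".

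The Statistical analysis section plans baseline comparisons by chi-square and t-test to see whether the arms are alike. The between-group comparison is a two-sample t-test, or a Mann-Whitney test if the data are skewed. No covariate is named. The note to Table 2 places the baseline assessment before allocation.

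The Sample size section derives the number "by considering the mFRT as the primary outcome measure". Trial status reports the trial completed in July 2025.

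**The concern.** A trial can deal with a prognostic factor by balancing it through the randomisation, by adjusting for it in the analysis, or both. As described, this trial does neither for baseline reach or for ASIA grade. Both plausibly predict seated reach after four weeks, although the article gives no figure for either.

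The baseline significance tests do not fill the gap. They say whether an imbalance is larger than chance would usually produce, they have little power at about 11 per arm, and they leave the treatment estimate unchanged.

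At stake are the precision and credibility of one small result. Outcome variation that baseline measurements could explain stays in the error term, and a visible imbalance would leave readers unsure how much of the observed difference reflects the starting point.

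**Working it through.** **1. The plan's own figure.** "The total sample size was calculated at 20"; then "The potential loss to attrition was estimated at 10%. Hence, the total sample size was 22". 20 × 1.10 = 22 reproduces the second step. The 20 cannot be reproduced, because no effect size is given. Solving the noncentral t for 10 per arm, two-sided α = 0.05 and 80% power gives d = 1.32. Effects from 1.32 to 1.41 all lead to N = 20 two-sided (1.16 to 1.23 if one-sided; sidedness is not stated). I use 1.32, the low end of the two-sided range.

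**2. Power of the planned test at 11:11.** Noncentrality = d × √(n₁n₂/(n₁+n₂)) = 1.325 × √5.5 = 3.11, with 20 df. Power = 84%.

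**3. Imbalance in a continuous baseline factor at exactly 11:11.** The standardised difference between arms has SE = √(2/11) = 0.426.
- More than 0.5 SD: 0.5/0.426 = 1.17, two-sided P = 24%.
- More than 0.25 SD: 0.25/0.426 = 0.586, two-sided P = 56%.

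**4. Imbalance in grade at exactly 11:11.** Assume 7 of 22 hold one grade. The number in one arm is hypergeometric(22, 7, 11). P(5:2 or worse) = 2 × (0.1490 + 0.0298 + 0.0019) = 36%. With 8 of 22, P(6:2 or worse) = 18%.

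A 5:2 split is a difference in share of 3/11 = 27 points. If that grade differs from the others by Δ = 1 within-grade SD on mFRT (assumed), the total SD is √(1 + (7/22)(15/22) × 1²) = 1.103. The unadjusted difference then moves by 0.273/1.103 = 0.25 total SD, or 0.13 to 0.34 for Δ of 0.5 to 1.5. Against d = 1.32, 0.25 is about a fifth.

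**5. Gain from adjusting for baseline mFRT.** Suppose d = 1.32 describes post-intervention mFRT, and baseline and final reach correlate at ρ (assumed). The residual SD shrinks by √(1 − ρ²), so noncentrality becomes 3.11/√(1 − ρ²), with 19 df.

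| ρ | √(1 − ρ²) | noncentrality | power |
|---|---|---|---|
| 0 | 1 | 3.11 | 84% |
| 0.3 | 0.954 | 3.26 | 87% |
| 0.5 | 0.866 | 3.59 | 93% |
| 0.7 | 0.714 | 4.35 | 98% |

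These figures take baseline means as equal. Chance imbalance inflates the variance of the adjusted estimate on average by 1 + 1/(22 − 4) = 19/18. Dividing the noncentrality by √(19/18) gives 85%, 91% and 98% for ρ of 0.3, 0.5 and 0.7. The gain remains but is small at ρ = 0.3; below about ρ = 0.25 it vanishes.

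**6. Arm sizes, only if the list were simple (not established).** Binomial(22, 0.5): P(11:11) = 17%, P(9:13 or worse) = 52%, P(8:14 or worse) = 29%. Power is 83% at 9:13, 81% at 8:14 and 79% at 7:15, and 82% on average: about 2 points below 11:11.

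**The case against.** A reader might infer from the Randomization section that the list was simple, so that arm sizes were left to luck and the stated equal allocation is contradicted. The documents do not support this. The section never says simple or unrestricted; a blocked list or a fixed 11:11 list fits both it and the equal allocation in Patient and study design. The Discussion sentence supports the view that *stratified* blocks were not used; it does not show that blocks were absent. A condensed article may also leave block details to the full protocol. Even under a simple list, step 6 shows a small loss.

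It can also be said that chance imbalance is not bias, that the t-test stays valid, and that between-grade variation is already inside the outcome SD. That is right. It limits the point to precision and credibility, but does not make the unadjusted test the better choice.

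The share of each grade, the effect of grade and ρ are all assumed. This stands, and it weakens the case for grade more than for baseline reach. With 7 of 22 in the grade and a 1 SD effect, adjusting without stratifying gives about 88.5% power at 11:11, against 89.9% with both and 84.0% with neither. With a 0.5 SD effect, adjusting without stratifying gains nothing (83.8%). Most of any gain therefore comes from adjustment, and stratifying the list adds little more than one point.

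Finally, the Abstract says effectiveness will be judged on changes in mFRT. If the t-test is applied to changes, baseline reach is partly handled. ANCOVA is still more precise: its residual variance is 1 − ρ² against 2(1 − ρ), which is 0.75 against 1.00 at ρ = 0.5 and 0.51 against 0.60 at ρ = 0.7. The Statistical analysis section does not say which quantity is tested.

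**Conclusion.** The point holds as one about the analysis. Severity is mixed among 22 participants, no stratification is described, and the between-group test is unadjusted. Sizeable chance imbalance is likely enough to plan for, even with arms of exactly 11: 24% for more than 0.5 SD on a continuous factor, and 36% for a 5:2 split or worse of a grade held by 7 of 22. The first figure needs only 11:11 and a roughly normal factor; the second rests on an assumed grade share.

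Adjusting for baseline mFRT would raise power from 84% to about 87-98%. This assumes d = 1.32 on post-intervention mFRT, a two-sided test and ρ of 0.3 to 0.7, none of which the article gives. The comparison is not biased on average, and neither a simple list nor unequal arms can be concluded from the text.

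**What to change.** In the Statistical analysis section, before unblinding, replace the unadjusted test for the primary outcome with an ANCOVA of post-intervention mFRT on group, adjusted for baseline mFRT and, if the numbers per grade allow, ASIA grade (B versus C/D). Say in advance what number counts as enough. State what takes the place of the Mann-Whitney route for this outcome, for example the same model on ranks. If the group comparison has already been seen, report the adjusted result beside the planned one and label it as added afterwards.

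State whether the list was simple, blocked or of fixed total, and report the realised arm sizes. The list itself cannot be changed, because the trial is complete.

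The cost is one degree of freedom per covariate, and a slight loss of precision if baseline turns out to be only weakly related to outcome. No new data are needed: baseline mFRT is collected before allocation, and ASIA grade is an eligibility item.
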